### 2.4. Recruitment and Informed Consent

Parents: All parents participating in the program are invited to participate in the current study through their key worker, however refusal to be in the study does not preclude them from receiving the FPR program. Due to the complexity of families and the need to have a trusting relationship established with the key worker, consent is likely to be obtained between the second and fourth months of program participation based on worker discretion. A flyer, written at a grade 5 literacy level and covering the most salient points of the study, is provided to all parents as they consider participating; declining participation has no effect on service delivery. After reading the flyer, an explanatory statement and consent form is provided (available on request), that requests approval for the receipt of the parent’s assessments and limited non-identifiable demographic data to be shared with the evaluation research team. For parents with children who are not adults, their legal guardian provides consent and the parent also needs to give assent. A separate explanatory statement and consent form have been developed for any parents who are interested in being interviewed during or post program participation.

MacKillop Family Services Staff: An explanatory statement and consent form is provided to all staff prior to participating in research activities like a focus group or interview. Choosing not to participate does not impact their current or future employment with MacKillop Family Services or their relationship with Monash University. Each of the nine teams comprises a team leader and approximately five key workers/practitioners. It is expected that the majority of staff will participate (*n* = 50 at minimum) as focus groups/interviews are being conducted during scheduled team meetings. Nonetheless, ongoing recruitment of staff will occur concurrently with data analysis so that saturation of themes can be assessed.

## 3. Data Collection

Figure 1 outlines the objectives, outcomes, and data being collected in the study, which is described in more detail below. While Figure 1 provides a snapshot of the outcomes and data, Table 1 offers specific details of all the data to be collected to answer the research objectives. All of the following assessments and administrative data are completed as part of standard practice of the MacKillop Family Services’ FPR program. Therefore, whilst data are collected for all families who engage in the FPR, only those who provide consent will have their data shared with the research team and included in the evaluation.

### 3.1. Outcome Measures for Objective 1–Effectiveness

#### 3.1.1. Parent and Family Focused Quantitative Measures

North Carolina Family Assessment Scale–for General Services and Reunification (NCFAS-GR) [26]:

The NCFAS-GR assesses change over time on ten family functioning domains that cover topics like safety, wellbeing, environment, and social life. The scale is completed by the FPR worker who accumulates knowledge about the family and then completes it in one sitting. Domain scores are measured using a six-point Likert scale ranging from “Serious Problem/Weakness = −3” to “Clear Strength = 2”. There is the option to provide a short comment to the score. The scores strongly guide the planning and practice, while also informing the child and family action plans and family goals. The NCFAS-GR is completed at the start of the program, after approximately 3 months or the middle, and upon closure. The NCFAS-GR has high internal consistency (*a* = 0.79–0.91) when implemented with families involved with Child Protection [27].

As per Figure 1, the NCFAS is being used to measure four of the five effectiveness objectives. The parental capability and self-sufficiency domains measure parent knowledge, parenting skills (i.e., sleep settling, developing routines, responding to cues, use of consequences etc) and parenting capability. The family safety and environment domains measure safety and security of the family’s home environment. Family interactions will be measured using the family interactions subscale of the NCFAS, which comprises eight items examining bonding with children, communication with children, expectations of children, relationship between parents/caregivers, support within the family, and family routines, rituals, and activities. The first three items provide an indicator of parent–child attachment, while the combination of all eight items yields an overall score of family interactions. The child wellbeing and family health domains examine the child’s health and development. In addition, the social life domain measures the child’s connection to education, as well as the parent’s connection to community services.

Parent Efficacy and Empowerment Measure (PEEM) [28]:

The PEEM is comprised of 20 positively framed statements about parenting that are rated by the parent on a scale from one to ten. The measure examines a parent’s feelings of control and confidence in parenting, especially when challenges present. Therefore, it is being used to determine the effectiveness of the FPR in improving parental confidence. The measure has been developed with an understanding of social work practice and information is available to support workers to use it appropriately, and it has high internal consistency (*a* = 0.92) [29]. Parents complete the PEEM during a session with their FPR worker, and it can be used as a tool to support disclosure and relationship building. The PEEM is completed at the start and upon closure by all families except for MST-Psych participants.

#### 3.1.2. Child Focused Quantitative Measures

Ages and Stages Questionnaire [30]: This screening tool, completed by the FPR worker, measures progress towards developmental milestones in children up to 60 months in age. All children up to five years of age are assessed using this measure. There are 21 measures based on age in months, each with items that are appropriate for the selected age, with high internal consistency (*a* = 0.86) [31]. As such, a different survey is used between baseline and closure depending on the child’s age. Scores indicate if the child needs referral to specialist services or extra monitoring. This measure is completed at the start of the program and upon conclusion.

Strengths and Difficulties Questionnaire (SDQ) [32]: The SDQ comprises 35 items about the psychosocial functioning and behaviour of the child, and hence responds to the FPR’s impact on child wellbeing. There are 25 statements rated as ‘not true’, ‘somewhat true’ or ‘certainly true’, five short answer questions and an additional five items, which rate the impact of the difficulties shown. This measure is used by parents about their children who are aged 6–9 in all metropolitan areas or for children aged 6–17 in regional areas as they are not receiving the MST-Psych program. Attempts are made to use the self-report youth measure for children over 10 years of age, however where this is not possible, the parent reports on the child’s behalf. Both versions have moderate to good internal consistency (*a* = 0.53–0.86) [33]. The SDQ is completed at the start and upon conclusion.

Child Behaviour Check List (CBCL) [34]: The MST-Psych program uses the Child Behaviour Checklist. This measure is completed by the parent and/or young person with the support of the FPR MST family therapist to outline problem behaviour in children and responds to the child behaviour objective. Respondents are invited to consider their own/their child’s behaviour in the last six months. There are eight individual syndrome scales with high internal consistency (a = 0.90–0.97) [35]. Two scales are derived by combining scores from some of the syndrome scales to determine internalising or externalising problems. Scores can be compared to a normative sample to determine the severity of the problem, which can be classified as normal, borderline or clinical. This checklist is completed at baseline and upon program closure.

Brief Symptom Inventory (BSI) [36]: The MST-Psych program also uses the BSI, which has 53 items that examine nine system areas of psychopathology, with each rated on a five-point Likert scale from 0 (not at all) to 4 (extremely). Respondents are invited to consider the intensity of their distress over the past 7 days, and the severity of the problems can be calculated. This measure is used to understand adolescent wellbeing and behaviour, with strong internal consistency (a = 0.93) [37]. The BSI is collected by the adolescent (aged 10–17 years) at baseline and upon program closure.

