## 4. Analytical Considerations

The primary quantitative outcome of this study is to examine the degree to which there are improvements in psychosocial outcomes among families who engage in the program. All completed questionnaires will be de-identified by a specific data aggregation worker who will assign a unique ID code (e.g., FPR003) to each family so that their data remain anonymous to the research team. Descriptive statistics will be calculated based on administrative and demographic data sourced from the referral form. Main caregiver complexity will be determined using the ACEs survey and the number of ACEs will be calculated. A series of paired sample t-tests (repeated measures) will be used to compare participants’ mean differences on the measures at the beginning and end of the program. Analysis of Variance will be employed to review the number of reports before, during and after the program to determine any statistical differences. The number of care episodes and time to reunification will be analysed descriptively. All analyses will be performed using the Statistical Package for the Social Sciences (SPSS) software.

All qualitative data will be analysed using thematic analysis [41]. Data collection and analysis will occur concurrently so that data saturation can be adequately assessed. All audio recordings will be transcribed verbatim and systematically coded. Following in-depth review of the coded data, independent themes will be identified and developed based on recurrent content reflecting the different aspects of program implementation. The process of refining and reviewing themes will be an iterative process until themes are representative of the most pertinent and recurrent aspects of the data.

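### The ASQ form changes between baseline and closure, but the planned paired t-test names no common scale, so its mean difference cannot be read as change in child development

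*Protocol article*

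**What the plan says.** **ASQ.** Section 3.1.2 describes it as a worker-completed screen that "measures progress towards developmental milestones in children up to 60 months in age". It adds: "There are 21 measures based on age in months, each with items that are appropriate for the selected age". It concludes that "a different survey is used between baseline and closure depending on the" child's age. The only reading of the result that it gives is categorical: "Scores indicate if the child needs referral to specialist services or extra monitoring".

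**SDQ and CBCL.** Of the SDQ, section 3.1.2 says: "This measure is used by parents about their children who are aged 6–9 in all metropolitan areas or for children aged 6–17 in regional areas". Over age 10, youth self-report is attempted, "however where this is not possible, the parent reports on the" child's behalf. The CBCL, used in the MST-Psych program, may be completed by the parent, the young person or both. The BSI is completed by the adolescent at baseline and at closure.

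**Analysis.** Section 4 plans a series of paired t-tests on participants' "mean differences on the measures at the beginning and end of the program". It names no ASQ score and no rule about informants.

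**Where the result is used.** Objective 1(iii) in section 1.3 includes child development, and Table 1 lists change in child development over time as an outcome. Table 1 assigns both the ASQ and the NCFAS child wellbeing and family health subscales to it.

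**The concern.** A paired t-test takes closure minus baseline for each child. The difference has a meaning only if both scores are on one scale. For the ASQ the protocol itself says the form, and with it the items, changes between the two occasions. If two forms place the same child at different levels, that gap enters the mean difference along with any real change. It can produce an apparent gain or loss, or hide a real one, and a pre-post study with no comparison group has nothing to subtract it against.

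The ASQ is the dedicated early-years instrument for a named effectiveness outcome. The conclusions in section 6 would treat significant baseline-to-closure improvement as strong support for scale-up.

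A lesser version of the problem could arise on the SDQ and CBCL if a parent answered at one time and the young person at the other.

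**Working it through.** **1. The plan's own figure.** The only sample-size figure is 98 families (section 2.3), from alpha 0.005, correlation 0.50 and power 0.95 on the NCFAS. No effect size is stated. For a one-group repeated-measures ANOVA with m occasions, the noncentrality is f² × n × m / (1 − ρ). With m = 3 (NCFAS at baseline, mid and closure) and an assumed f = 0.20, it is 0.04 × 98 × 3 / 0.5 = 23.52. Power is then 0.951 at n = 98 and 0.949 at n = 97, so 98 is reproduced. It does not involve the ASQ, SDQ or CBCL and is not affected.

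**2. How often the form changes.** Section 3.1.2 says that it does. As a rough check, if the 21 forms were evenly spaced over 60 months (an assumption), each would cover 60 / 21 = 2.86 months. Section 1.2 expects about six months of engagement, and up to a year. Six months is 6 / 2.86 = 2.1 forms, so nearly every pair would cross forms.

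**3. What a form effect would do.** The documents give no offset between forms, so this is an illustration only. Assume no true change, unit SD on each form, every pair changing form, correlation 0.3 across forms, and an average offset d between forms.

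- SD of the difference = √(2 × (1 − 0.3)) = 1.183.
- Noncentrality = √n × d / 1.183. For n = 98 and d = 0.3: 9.90 × 0.254 = 2.51.

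Probability that the two-sided test rejects although no child has changed:

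| Pairs | Alpha | d = 0.2 | d = 0.3 | d = 0.5 |
|---|---|---|---|---|
| 98 | 0.05 | 0.381 | 0.700 | 0.985 |
| 98 | 0.005 | 0.122 | 0.364 | 0.902 |
| 60 | 0.05 | 0.251 | 0.489 | 0.896 |
| 30 | 0.05 | 0.146 | 0.269 | 0.609 |

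The smaller rows are shown because the ASQ covers only children up to five, and the article does not say how many that will be. The apparent change equals d whatever the number of pairs. If offsets differ in sign between form pairs they partly cancel, and d is what remains on average.

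**4. What informant switching could do (SDQ over age 10, CBCL).** The documents give neither a switching rate nor an offset. Assume a share s of pairs switches, all in one direction, with correlation 0.5 for unswitched and 0.3 for switched pairs. The apparent change is s × d, and the variance of the difference is 1.4s + 1.0(1 − s) + s(1 − s)d².

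- s = 0.10, d = 0.2 to 0.5: apparent change 0.02 to 0.05 SD; rejection 0.054 to 0.076 (n = 98, alpha 0.05).
- s = 0.25, d = 0.2 to 0.5: apparent change 0.05 to 0.125 SD; rejection 0.075 to 0.208.

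Switches in opposite directions would partly cancel.

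**The case against.** The strongest defence is that section 4 nowhere says raw ASQ totals will be subtracted. Each form suits the child's age, and repeating one form would bring in maturation, so changing the form is proper use of the instrument. The article is condensed, and the exact score could be named in a fuller plan.

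Much of this stands. A reader might infer that raw scores are subtracted and that the result is bound to be uninterpretable; the documents do not say so, and an age-referenced score would be comparable across forms. But the article does more than stay silent. It says the form changes, fixes a paired mean difference, and describes the ASQ result only by referral or monitoring status, which the t-test as worded does not use. Those statements need to be joined up.

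Three further readings are tempting but unsupported.

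- **All the child behaviour tests compare unlike scores.** The BSI has the same respondent at both times. SDQ self-report is attempted only over age 10, which on the stated age ranges means mainly the regional sites. The text describes how an informant is chosen, not a switch within a child, and the CBCL wording may mean parallel reports.
- **Objective 1(iii) as a whole fails.** The NCFAS child domains also address it, on one fixed scale at baseline, mid and closure.
- **Children who pass 60 months during the program add to the problem.** They give a missing pair, not a pair of unlike scores, and the documents give no age distribution from which to size this.

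**Conclusion.** The point holds for the ASQ. With a form that changes and no common scale named, the paired mean difference cannot be read as change in child development unless an age-referenced result is specified. That follows from sections 3.1.2 and 4 alone. Its size cannot be derived from the documents: the rejection rates of 0.381 to 0.985 (98 pairs, alpha 0.05) rest on assumed offsets of 0.2 to 0.5 SD, an assumed correlation of 0.3 and every pair changing form.

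For the SDQ over age 10 and the CBCL, the text permits a change of informant but does not state that one occurs. The size is unknown, and under the assumptions above it is small to moderate. This is a precaution, secondary to the ASQ point.

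The NCFAS child domains, the BSI and the sample size of 98 are unaffected. The change should be made, but it does not threaten the study as a whole.

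**What to change.** **ASQ.** State in section 4 that the ASQ is compared on an age-referenced result, in one of two ways:

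- each score's distance from the cut-off of the form used, kept in the planned paired t-test; or
- change in category (on track, monitor, refer) with a paired categorical test.

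No ordinal or logistic model is required. Neither option needs new data, since the forms already yield a referral or monitoring result. Categories cost some precision. Distance from the cut-off keeps more, but it aligns the forms in level and not necessarily in spread, which should be acknowledged.

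**SDQ and CBCL.** Record who answered at each time, form pre-post pairs only from the same informant, and analyse parent and youth reports separately. Where practicable, ask workers to return to the baseline informant at closure. The cost is the loss of any switched pairs and smaller groups. If switching is related to how the family is doing, leaving those pairs out could also introduce selection, so their number should be reported. Assessments are already routine for all families in the program, so a worker instruction may reach only later closures; the analysis rule can still apply to all pairs whose informant is known.

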The MacKillop key worker/practitioner engages with the family intensively, defined as a home visit for at least one hour, three times a week, or less visits and regular phone contact plus other activities as required. The timing of these visits is flexible to accommodate the needs of families. Funding is provided to allow for 200 hours of work with an additional 40 hours of step-down towards closure. It is expected that families will engage with the program for approximately six months, but this could last for up to a year. The most practical caseload per full time practitioner is four families, however workers may hold up to six families, albeit at a decreased intensity and with less fidelity to the model. In general, workers focus on reducing stressors and barriers to health and family functioning, such as housing, and offer referrals to specialist services if needed. Workers also focus on the interactions within the family and strengthen core life skills.

For families who are subject to an unborn report (reported to CP while pregnant) or with children aged 0–9, workers use evidence informed methods that focus on parenting skills (i.e., sleep settling, developing routines, responding to cues, use of consequences etc), parent–child attachment, and capacity to effectively respond during a crisis, such as those from the newborn behavioural observation method [20] or circle of security program [21]. These methods support families to meet their goals and mitigate risk. Specifically, the brokerage is a crucial component of the program that helps to fund items that meet families’ immediate or essential needs (i.e., groceries, rent), or can support families to achieve their goals (i.e., fund mental health or substance use counselling). As participation is voluntary and no specific incentives are provided, the brokerage may often be viewed by families as an incentive to engage in the program.

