## Figures and Tables

**Figure 1 ijerph-18-10279-f001:**
[figure not shown]
Outcomes and measures to evaluate the effectiveness and implementation of FPR. Note. NCFAS = North Carolina Family Assessment Scale; PEEM = Parent Efficacy and Empowerment Measure; MARAM = Family Violence Multi-Agency Risk Assessment and Management Framework; ASQ = Ages and Stages Questionnaire; SDQ = Strengths and Difficulties Questionnaire; CBCL = Child Behaviour Check List; BSI = Brief Symptom Inventory.

**Table 1 ijerph-18-10279-t001:** Effectiveness and implementation outcome measures.

Outcome	Individual Measures	How Measured	When Measured
	Program Effectiveness Outcomes		
Parental knowledge, skills, and confidence	Self-efficacy and empowerment Parenting capability and self-sufficiency	Connection form—parent strengths and capacity section; PEEM; NCFAS-parental capability and self-sufficiency subscales	NCFAS at baseline, mid and closure; PEEM at baseline and closure
Family safety and home environment	Recent family violence screens (MARAM) Child protection notifications OOHC entry/re-entry	Connection form NCFAS—family safety subscale, environment subscale MARAM—intermediate screen Linked data from the Victorian Government	NCFAS at baseline, mid and closure; MARAM at intake
Child development (early years) or behavior (adolescence), relationships and education	Looking at changes in child development over time Is there a good parent/child relationship What is the child’s connection to education	NCFAS—Child Wellbeing, Family health subscales, Family interactions; ASQ—Child development up to 60 months SDQ—Adolescent Behaviour (regional) CBCL—Adolescent Behaviour (metro) BSI—Adolescent Behaviour (metro) Connection form; Closure checklist; Closure goals; Client interviews and exit survey	NCFAS at baseline, mid and closure. Others at intake and closure
Connection to services and culture	Are Aboriginal and Torres Strait Islander families supported in their cultural connection.	Connection form; NCFAS—social life subscale; Closure checklist; Cultural support plan of Aboriginal and Torres Strait Islander children are provided; Families are connected to cultural communities; Staff have cultural training and access to a cultural advisor	NCFAS at baseline, mid and closure. Baseline for connection form; and closure for closure checklist

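### The stated age limits leave children between 60 months and 6 years without an ASQ or SDQ, and children near 60 months at intake can lose their pair before closure

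*Protocol article*

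**What the plan says.** The study covers families with children aged 0 to 17 (section 2.3). Section 3.1.2 allocates the child questionnaires by age:

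- **ASQ.** It "measures progress towards developmental milestones in children up to 60 months in age", and Table 1 repeats the limit: "ASQ—Child development up to 60 months". The next sentence of section 3.1.2 states coverage in years: "All children up to five years of age are assessed using this measure". Timing: "This measure is completed at the start of the program and upon conclusion". The form changes as the child grows ("a different survey is used between baseline and closure"), but no form is described above 60 months.
- **SDQ.** It is for "children who are aged 6–9 in all metropolitan areas or for children aged 6–17 in regional areas", also at start and conclusion. Table 1 lists it only as "SDQ—Adolescent Behaviour (regional)".
- **CBCL and BSI.** These belong to MST-Psych, which section 1.2 places in metropolitan areas for ages 10 to 17.

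On the interval between the two assessments, section 1.2 says: "It is expected that families will engage with the program for approximately six months, but this could last for up to a year". It adds that some families with young children may receive a further 240-hour episode. Section 4 compares start with end on each measure by paired t-tests.

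**The concern.** A paired test uses a child only if the same instrument is completed at both time points. The age limits can break that in two ways. First, the ASQ ends at 60 months and the SDQ starts at 72, so the year between has no child questionnaire. Second, the ASQ limit is a fixed age while the child keeps ageing through the program. A child who starts on the ASQ shortly before 60 months may be too old for it at closure, and has no SDQ baseline to pair with a later SDQ.

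The losses are tied to age and to program length, so they are not random. They fall on the group around school entry. Data not collected at intake cannot be recovered by any later analysis plan. Separately, staff working from Table 1 would not learn that 6- to 9-year-olds should have an SDQ.

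**Working it through.** **Inputs from the protocol article.** ASQ ceiling 60 months (section 3.1.2, Table 1). SDQ floor 6 years = 72 months (section 3.1.2). Baseline-to-closure time D about 6 months, up to 12 (section 1.2). The article gives no figure for the share of children with a pair, so there is none to reproduce.

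**Input assumed.** The age distribution of children is not given. Even spread over 0 to 72 months is used first, then varied. Each result treats every program as having the same length D.

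**Step 1: who lacks a pair on the strict reading.** A child under 72 months at intake has an ASQ pair only if intake age + D ≤ 60. Those with intake age above 60 − D have no pair, a window of 72 − (60 − D) = 12 + D months.

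- D = 6: (12 + 6)/72 = 18/72 = 25.0%
- D = 12: (12 + 12)/72 = 24/72 = 33.3%

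Of this, the 60-to-72-month hole is 12/72 = 16.7%. Outgrowing the ASQ adds 6/72 = 8.3% to 12/72 = 16.7%.

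**Step 2: the wider reading.** If the years-of-age sentence includes five-year-olds, the ASQ runs to 72 months in practice and only outgrowing remains: D/72, that is 6/72 = 8.3% to 12/72 = 16.7%. This reading uses the ASQ past the 60-month limit stated one sentence earlier.

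**Step 3: other age mixes, strict reading, D = 6 to D = 12.**

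| Assumed mix under 6 years | Share without an ASQ or SDQ pair |
|---|---|
| Even | 25.0% to 33.3% |
| Infants under 12 months double-weighted: 18/84 to 24/84 | 21.4% to 28.6% |
| Infants triple-weighted: 18/96 to 24/96 | 18.8% to 25.0% |
| Linear decline to half at 72 months: 10.125/54 to 14/54 | 18.8% to 25.9% |
| Linear decline to zero at 72 months: (18/72)² to (24/72)² | 6.3% to 11.1% |
| Older-weighted, doubling linearly from 0 to 72 months: 16.875/54 to 22/54 | 31.3% to 40.7% |

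**Step 4: share of all children.** With ages even over 0 to 17 (18 × 12 = 216 months), the strict reading gives 18/216 = 8.3% to 24/216 = 11.1%.

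**Step 5: Table 1 against section 3.1.2.** The text assigns the SDQ to ages 6 to 9 in metropolitan areas and 6 to 17 in regional areas. The Table 1 label covers regional adolescents only. The 6- to 9-year-olds are missing from it in both settings.

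**The case against.** **The bands may be meant to adjoin.** The years-of-age sentence for the ASQ, followed by an SDQ starting at 6, can be read as 0 to 5 and then 6 upward. On that reading every five-year-old is assigned a measure. The reading is fair, and it cuts the illustrative share to 8% to 17%. It does not clear the plan, because it contradicts the 60-month limit given in the same paragraph and in Table 1. One of the two statements has to change.

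**The size is not known.** A reader might take a quarter to a third as a ceiling or an estimate. The documents support neither. It needs evenly spread ages and the strict reading, and 33% also needs every program to last a full year, whereas about six months is expected. The program accepts unborn reports, and an infant-heavy intake would lower the share. This objection stands in full.

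**The child outcome has another source.** A reader might infer that objective 1(iii) rests only on the children who keep a pair. It does not. Section 3.1.1 uses the NCFAS-GR child wellbeing and family health domains for child health and development, and Table 1 schedules them at baseline, mid-program and closure with no age limit. The sample size also rests on the NCFAS (section 2.3). The reply is limited: the NCFAS-GR is a family-functioning scale rated by the worker delivering the program, so it replaces neither the ASQ's milestone content nor the SDQ's parent report.

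**Metropolitan children who turn 10.** A reader might infer that a child who starts the SDQ at 9 loses it at the tenth birthday. The article states no such rule. It ties the age split to program stream and says nothing about a child changing stream mid-program. This is at most a point to clarify.

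**Longer programs and harder cases.** A reader might also suppose that the children lost are the more difficult families. Longer programs do raise the chance of crossing 60 months, but nothing in the article links length to severity.

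**Conclusion.** The point holds in a limited form. On the stated limits, children over 60 months and under 6 years have no ASQ or SDQ, and the only reading that gives them one conflicts with the 60-month limit. Children close to 60 months at intake can also outgrow the ASQ before closure and end with no pair on either instrument.

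The size depends on an age distribution that the article does not give. With even ages under 6, the share without a pair is 25% to 33% on the strict reading and 8% to 17% on the wider one. The other mixes tried run from about 6% to 41% on the strict reading. The consequence is a loss of child-specific questionnaire data in one age band for objective 1(iii), while the NCFAS-GR domains remain. The Table 1 label is a plain inconsistency that needs no assumption. Because the matter decides which data are collected, it is worth correcting now, as a cheap improvement and not as a flaw that undermines the evaluation.

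**What to change.** 1. Reconcile the two ASQ age statements in section 3.1.2 so that one upper limit, in months, applies throughout and in Table 1.
2. Start the SDQ where the ASQ range ends instead of at age 6, once the sponsor has confirmed that its SDQ version covers those ages.
3. Subject to the same confirmation, give the SDQ at intake and closure, alongside the ASQ, to children who could pass 60 months before closure. With a one-year maximum, that means children aged 60 − 12 = 48 months or older at intake.
4. Report ASQ pairs as available only for children still within the ASQ range at closure. An SDQ pair measures psychosocial functioning and behaviour, so it does not stand in for a developmental pair. Carrying the ASQ past its limit is not a solution either.
5. Correct the SDQ entry in Table 1 to the metropolitan (to age 9) and regional (to age 17) bands of section 3.1.2, with the new lower age.
6. As a clarification only, state that a metropolitan child who starts on the SDQ at age 9 keeps it at closure.

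The cost is protocol wording, a few more minutes per affected family for a questionnaire the service already uses, and a small change to routine assessment across the nine sites.
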